#### Groups:

1.3.1

The participants will be randomly allocated to the following groups:

Group 1: control—absence of bruxism.Group 2: bruxism treated with infrared LED.Group 3: bruxism treated with occlusal splint.

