**Methods::**

The participants will be 76 children, which will be randomly allocated to a control group, that is group 1, absence of bruxism; group 2, children with bruxism treated with infrared light-emitting diode (LED); and group 3, bruxism treated with occlusal splint. All participants will be submitted to a clinical evaluation to evaluate muscle activity and salivary biomarkers, before and after treatments. Muscle activity will be verified by electromyography of muscles mastication, masseter and temporal, and salivary biomarkers observed will be cortisol and dopamine levels.

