### Inclusion criteria

1.1

The sample will be composed of children in the mixed dentition phase (permanent incisors and molars erupted) and adolescents with an established permanent dentition.

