### Allocation procedure

1.3

Block randomization (groups of 4 participants) will be performed using sequentially numbered (1–76) opaque envelopes. The contents of the envelopes will be determined randomly with the aid of a computer program. Each envelope will contain a piece of paper stipulating the group to which the child/adolescent will be allocated. The envelopes will be sealed until the time of treatment.

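### The no-bruxism control group is described as randomly allocated, but disease status cannot be assigned, so no contrast with Group 1 is a randomised treatment comparison

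*Protocol article*

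**What the plan says.** Section 1.3.1 (Groups) states: "The participants will be randomly allocated to the following groups". Three groups follow. The first is "Group 1: control—absence of bruxism"; the other two are children with bruxism treated with infrared LED or with an occlusal splint. The Abstract (Methods) repeats this for the full sample of 76, who are to be "randomly allocated to a control group, that is group 1, absence of bruxism", or to one of the two treated groups.

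Section 1.3 (Allocation procedure) gives the mechanism: "Block randomization (groups of 4 participants) will be performed using sequentially numbered (1–76) opaque envelopes". It continues: "Each envelope will contain a piece of paper stipulating the group to which the child/adolescent will be allocated". It also says: "The envelopes will be sealed until the time of treatment".

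Section 1.4 (Evaluation of bruxism) bases the diagnosis on caregiver report and clinical signs. Section 1.1 (Inclusion criteria) defines the sample by dentition and does not mention bruxism. Section 1.8 (Analysis of results) plans one two-way mixed ANOVA for the treatment effect on muscle activity and salivary markers, and does not separate randomised from non-randomised contrasts.

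**The concern.** Group 1 is defined by a characteristic of the child and not by something the trial assigns. A child with bruxism cannot be allocated to not having it, and a child without it does not fit either treated group. The article nevertheless describes one randomisation covering every participant and every group.

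Two things are at stake. The first is inference. A reader of the Abstract would take Group 1 for a randomised control and would read a difference from it as a treatment effect, although the children differ in disease status by design. The second is conduct. Staff who follow the allocation text literally would open envelopes whose contents do not fit the child.

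**Working it through.** **1. Does the envelope list cover the whole sample, Group 1 included?**

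Inputs from section 3 (Material and methods): 16 per group, 20% added for dropout, 19 per group, 76 in total.

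- 16 × 1.2 = 19.2, taken as 19.
- 19 × 4 = 76, the stated total and the number of envelopes.
- 19 × 3 = 57, so 76 is not reached with the three groups of section 1.3.1.

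The figure 76 is therefore reproduced only with four groups. That agrees with section 1.5 (Photobiomodulation treatment protocol), which describes red LED, infrared LED and a splint as Groups 2, 3 and 4 and so leaves Group 1 as the fourth. Blocks of 4 fit the same count: 76 / 4 = 19 blocks. The list includes places for the no-bruxism group. If only children with bruxism were randomised, the number of envelopes would be:

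| Active arms | Envelopes at 19 per arm | Group 1, not randomised | Total |
|---|---|---|---|
| Two (section 1.3.1) | 2 × 19 = 38 | 19 | 57 |
| Three (section 1.5) | 3 × 19 = 57 | 19 | 76 |

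Neither case needs 76 envelopes.

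**2. Is the problem resolved elsewhere in the article?**

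Section 1.4 makes bruxism a diagnosis that precedes allocation. No section confines randomisation to children with bruxism, describes separate recruitment of controls, or defines an untreated or sham-treated group with bruxism.

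**3. What does a contrast with Group 1 estimate?**

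Take the reading most favourable to the plan, in which the treatment effect is the group-by-time term. For a treated arm T against Group 1 it is

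(post_T − pre_T) − (post_1 − pre_1) = treatment effect + (untreated change with bruxism − untreated change without bruxism).

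A baseline gap that stays constant cancels. The second bracket does not. It contains regression to the mean in children selected for the condition, as far as the outcomes go with that selection, and any difference in natural course. With no untreated bruxism arm, the trial cannot estimate it. Between two arms randomised among children with bruxism, the corresponding bracket is zero in expectation.

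**4. How often would an envelope contradict the child's status if the text were followed literally?**

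Let p be the share of enrolled children with bruxism (not given, so assumed) and k the number of equal groups, one of them Group 1. A child with bruxism draws Group 1 with probability 1/k; a child without it draws a treated group with probability (k − 1)/k.

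Mismatch = p × 1/k + (1 − p) × (k − 1)/k

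| Assumed p | k = 3 | k = 4 |
|---|---|---|
| 10% | 0.033 + 0.600 = 63% | 0.025 + 0.675 = 70% |
| 50% | 0.167 + 0.333 = 50% | 0.125 + 0.375 = 50% |
| 100% | 0.333 + 0 = 33% | 0.250 + 0 = 25% |

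The k = 3 column assumes equal groups, which the stated design cannot deliver exactly: a block of 4 does not divide by three, and 76 / 3 = 25.3.

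**The case against.** The strongest defence is that the wording is careless and the design behind it is ordinary: a healthy reference group alongside randomised bruxism arms. The title and the Aim place the question in children with bruxism, section 1.3.1 describes the treated groups as having bruxism, envelopes stay closed until treatment, and section 1.5 gives Group 1 no treatment. A healthy reference group is legitimate. The planned analysis uses measurements before and after treatment, and section 1.8 names no specific contrast of LED with Group 1. The bare inclusion criterion may also be a product of condensing a longer protocol.

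Much of this stands, and it limits the point in three ways.

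- A reader might infer that children without bruxism will be given LED or a splint, and so see a safety problem. The document does not support that as an expected event, because the definitions of the treated groups resist it. It is a risk created by the allocation wording.
- A reader might infer that the whole trial is confounded. It is not: comparisons among the treated arms can be validly randomised if the envelopes are used only within children with bruxism.
- A reader might take the mismatch percentages as a measure of bias. They count envelopes that do not fit the child under an assumed share, and nothing more.

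The defence does not remove the contradiction itself. The Abstract and section 1.3.1 both say that Group 1 is randomly allocated, and envelopes for all 76 participants match that statement and not the charitable reading. The missing bruxism criterion in section 1.1 is context only; the point does not depend on it.

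**Conclusion.** The point holds as a contradiction in the stated allocation, with a definite limit on what Group 1 can show. The article says that all participants are randomised among groups, one of which is defined by not having the disease; that cannot be done, and no section corrects it. A contrast with Group 1 is non-randomised even after baseline is subtracted, and it should not be read as a treatment effect.

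This conclusion rests on the text alone and needs no assumed figure. The range of 33–63% of envelopes (three equal groups) or 25–70% (four) depends on assumed bruxism shares of 10% to 100% and on literal use of the list, so it is an illustration. The size of any bias in the Group 1 contrast cannot be worked out from the document. Because analysis cannot turn Group 1 into a randomised control, the allocation statement needs correcting.

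**What to change.** 1. Reconcile the number of active arms first. Section 1.3.1 lists infrared LED and splint; section 1.5 describes red LED, infrared LED and splint under different group numbers; the total of 76 equals 4 × 19. The sponsor must settle which is meant.
2. Make bruxism, as diagnosed under section 1.4, an entry criterion for the randomised part.
3. Prepare envelopes for children with bruxism only: 38 for two arms or 57 for three, at 19 per group. Use block sizes that are multiples of the number of active arms; a block of 4 cannot balance three.
4. Recruit Group 1 separately, and call it a non-randomised reference group in the Abstract and in section 1.3.1.
5. State in section 1.8 that treatment-effect claims rest only on comparisons among the randomised bruxism arms, and that comparisons with Group 1 are descriptive.

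The cost is revised wording and a new computer-generated list, with no added participants or procedures. The downside is that Group 1 loses the label of randomised control.

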### Evaluation of bruxism

1.4

The diagnosis will be based on the reports of parents/caregivers regarding the occurrence of grinding the teeth. For such, parents/caregivers will receive a patient history questionnaire to fill out and deliver to the school. The following clinical signs will also be investigated for the diagnosis: abnormal tooth wear on functional cusps of the teeth, tooth marks on tongue, linea alba on the buccal mucosa along the occlusal plane, gingival recession, mandibular and/or maxillary torus, fractures, and/or cracks on the teeth.^[12]^

### Photobiomodulation treatment protocol

1.5

The volunteers in Group 2 will be submitted to the initial evaluation of the morphological and psychosocial variables. During the same appointment, red LED (3 × 6 cm) will be administered using a board with 6 LEDs with a wavelength of 650 ± 20 nm, 7-minute operation time, optical spot of 5 ± 2 mm, and optical output of 2∼5 mW, with a dose of 2.675 J/cm^2^. Further analyses will be performed immediately after the photobiomodulation session and 1 week later. Group 3 will be submitted to the same analyses using an infrared LED protocol (wavelength: 850 ± 20 nm) with the same dose of 2.675 J/cm^2^.

The volunteers in Group 4 will be treated using the standard protocol of a rigid occlusal splint. After the initial evaluation, molds will be made for the fabrication of the splints, which will be delivered 1 week later. Written and verbal instructions for use will be given. After 1 month of daily use, the volunteers will return for the final morphological and psychosocial evaluations.

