### Protocol for electromyographic evaluation

1.6

Electromyography will be performed to complement the evaluation of the morphological aspects of the groups. The masseter and temporal muscles will be evaluated using a portable electromyograph (BTS TMJOINT) with wireless electrodes. The participant will be seated with Camper plane parallel to the floor. Three readings will be made on both sides with the muscles at rest, during habitual maximum intercuspation (isometric contraction), and during simulated chewing with Parafilm (isotonic contraction). The signal will be captured for 10 seconds under each condition. The first chewing cycle will be discarded and the subsequent 5 cycles will be collected.

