### Analysis of results

1.8

Data will be statistically analyzed using SPSS 24.0 software (IBM Corp., NY), considering an alpha level of 5%, by one of the authors ([name], Applied Statistics Specialist). The exploratory statistics will consist of means, standard deviation, medians, and quartiles. Normality will be tested by Shapiro–Wilk test and Quantilequantile-plot (QQ-plot) analysis. Those variables that do not show normal distribution will be transformed by the natural logarithm (ln).

A general linear model—2-way mixed model analysis of variance (ANOVA)—will be used to test the treatment effect in the observed variance of muscle activity and levels of salivary markers (considered as dependent variables). The effect size (partial Eta squared) and the power of the test for each model will also be obtained. The results of the Mauchley sphericity test and Levene equality of variances will be evaluated as ANOVA premises; when necessary, the Huynh-Feldt correction will be applied.

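### The LED and splint arms share no stated post-baseline assessment time, so the between-arm treatment effect is confounded with elapsed time

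*Protocol article*

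**What the plan says.** The timing is in the Protocol article, section 1.5 (Photobiomodulation treatment protocol).

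- **LED.** Treatment is given at the baseline visit: "During the same appointment, red LED (3 × 6 cm) will be administered". Then: "Further analyses will be performed immediately after the photobiomodulation session and 1 week later". A second LED group follows the same schedule: "Group 3 will be submitted to the same analyses using an infrared LED protocol". No later LED reading is described.
- **Splint.** "After the initial evaluation, molds will be made for the fabrication of the splints, which will be delivered 1 week later". Then: "After 1 month of daily use, the volunteers will return for the final morphological and psychosocial evaluations". No reading between baseline and that visit is described.
- **Group 1 (no bruxism).** No follow-up time is given in this section.

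Section 1.6 ties muscle activity to these evaluations: "Electromyography will be performed to complement the evaluation of the morphological aspects of the groups". Saliva is dated only in the abstract, as before and after treatment. Section 1.8 (Analysis of results) plans a two-way mixed ANOVA, which "will be used to test the treatment effect in the observed variance of muscle activity and levels of salivary markers". It does not say which visits form the time factor.

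**The concern.** A group-by-time ANOVA attributes a between-group difference in change to treatment only if the groups are measured at the same times. Here the after reading means minutes or 1 week in the LED arm and about 5 weeks in the splint arm. Anything that moves electromyographic or salivary values over those weeks enters the LED-versus-splint contrast as though it were a treatment effect. So does any waning of an LED effect that has not yet shown at 1 week.

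This cannot be repaired at analysis. At the final reading every LED child is at one elapsed time and every splint child at another, so no covariate or correction can separate the two. Group 1 cannot supply the correction either. Its follow-up is undated, and children without bruxism need not share the time course of children with it.

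**Working it through.** The document states no elapsed-time figure, so there is none to reproduce. All timing inputs come from section 1.5.

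**Step 1. Calendar.** One month is taken as 28 to 31 days.

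| | LED | Splint |
|---|---|---|
| Baseline | day 0 | day 0 |
| Treatment starts | day 0 | day 7 |
| Readings after baseline | day 0 (immediate), day 7 | 7 + 28 to 7 + 31 = day 35 to 38 |
| Last reading, from baseline | 1.0 week | 35/7 to 38/7 = 5.0 to 5.4 weeks |
| Last reading, from treatment start | 7 days | 28 to 31 days |

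The gap between last readings is 28 to 31 days. The ratio is about 5 counted from baseline and about 4 counted from the start of treatment. Baseline is the only time common to both arms in the text.

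**Step 2. What the planned model can do with these readings.**

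- *Two levels (before, after).* This can be fitted in every group that has both readings, but the after level mixes day 0 or day 7 (LED) with day 35 to 38 (splint).
- *Three levels.* Section 1.8 plans a sphericity test and a Huynh-Feldt correction, which matter only with three or more within-subject levels. LED has three readings (0, immediate, 1 week) and splint has two. A complete-case analysis on three time levels would drop every splint child.

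Neither gives a like-for-like treatment effect.

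**Step 3. Number of LED groups.** The abstract and section 1.3.1 list one infrared LED group, with the splint as Group 3. Section 1.5 describes a red and an infrared LED group, with the splint as Group 4. These passages need to be reconciled, but both LED groups in section 1.5 have the same schedule, so the timing gap is the same under either layout.

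**Step 4. Illustration only.** Assume a linear drift common to all arms, no treatment effect, and an SD of change of 1. None of this is in the document.

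- Bias = drift per week × gap in weeks, with gap = 30/7 = 4.29 weeks.
- 0.02 × 4.29 = 0.09 SD; 0.10 × 4.29 = 0.43 SD.
- Two-sided false-positive rate = Φ(b/se − 1.96) + Φ(−b/se − 1.96), with se = √(2/n).
- At b = 0.43: n = 16 gives se = 0.354 and a rate of about 23%; n = 19 gives se = 0.324 and about 26%.
- At b = 0.09 the rate is about 6% at either n, against a nominal 5%.

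**The case against.** The strongest reply is that the schedule may be incomplete as shown. The SPIRIT figure and the flowchart are not reproduced here and could list further visits. Section 1.5 calls only the splint evaluation final and excludes no interim splint reading. This limits certainty about the full visit grid, but the text that describes each arm gives no common time. If the figures do show one, sections 1.5 and 1.8 should say so.

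A second reply is that reading each treatment at the end of its own course can be a deliberate strategy, since one described LED session and a month of splint use differ in kind. That is fair, but the document does not state it, and the contrast would still be confounded with time.

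A reader might infer three stronger things that the document does not support:

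- *That the ANOVA cannot be fitted.* A two-level before/after factor can be. The trouble is what it compares.
- *That the bias has a known size.* No drift rate, form or direction is given. Regression to the mean would appear largely at the first re-reading in every arm, familiarisation follows the number of sessions more than weeks, and growth over about 4 weeks is likely small. The 1 SD planning difference in section 3 (2 with SD 2) concerns signs and symptoms of temporomandibular disorder, so it is not a yardstick for electromyography, cortisol or dopamine.
- *That the gap is equally established for saliva.* Saliva visits are not dated separately. The gap follows only if saliva is taken at the same visits.

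**Conclusion.** The point holds. On the stated schedule the last LED reading is at about 1 week and the splint arm's only post-treatment reading at about 5 weeks after baseline, with no shared post-baseline time. The between-arm treatment effect is therefore fully confounded with elapsed time, whatever the drift turns out to be. This rests on section 1.5 being the complete schedule and on the second factor of the ANOVA being time, which is the natural reading of section 1.8 but not its wording. The conclusion is firmest for electromyography. The 0.09 to 0.43 SD range shows only that the effect could run from negligible to material. It is not an estimate. The matter should be settled before data collection, because a missing common time point cannot be recovered afterwards.

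**What to change.** Change measurement times only and leave every treatment schedule as it is.

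1. In the splint arm, take electromyography and saliva at the existing 1-week delivery visit, before the splint is fitted. Measure Group 1 at 1 week too. The 1-week LED reading is then set against still-untreated children with bruxism at the same elapsed time.
2. Keep the 1-week LED reading. Where feasible, add a later LED and Group 1 reading at the time of the splint arm's final visit.
3. State in section 1.8 which visits form the time factor, and compare arms only at common times. Report the immediate post-session LED reading as a within-arm result.
4. If no later LED reading is taken, report the splint 1-month result as within-arm and make no LED-versus-splint efficacy claim from it.

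**Cost.** One extra set of electromyography and saliva measurements at a visit that already takes place, a 1-week reading in Group 1 if none is planned, and possibly one later visit for LED and Group 1. Each saliva collection carries the 24-hour restrictions of section 1.7. At the later common time the arms would also differ in time since treatment: LED children would be about 5 weeks past the described session, while splint children would have just completed a month of daily use. The protocol should state this as a limit on that comparison.

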## Material and methods

3

This project was evaluated by the human research ethics committee of University Nove de Julho (certificate of approval: 1.333.636) and clinical trials ID NCT03710174. The sample size was calculated considering α = 0.05 and an 80% power (n = 16 per group), to which 20% will be added to compensate for possible dropouts (n = 19 per group), totaling 76 children and adolescents. Additionally, sample size was calculated for internal validity by using the results of a previous study that evaluated the decrease in signs and symptoms of TMD after occlusal splint therapy (Restrepo et al^[15]^). Considering a mean difference between treatments equal to 2 (SD = 2), 3 groups, power of test of 80%, and an alpha level of 0.05, a minimum of 30 subjects should be included in each group.

The protocol is in accordance with the 2013 SPIRIT (Standard Protocol Items: Recommendations for Interventional Trials) Statement. The SPIRIT checklist can be found as an additional file and Figure 1 is the SPIRIT figure. SPIRIT was developed to provide guidance in the form of a checklist of recommended items to include in a clinical trial protocol, to help improve its content and quality (Fig. 2).

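### The group list has three groups, but the treatment section describes a red-LED arm and a Group 4, and 76 children at 19 per group fits only four groups

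*Protocol article*

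**What the plan says.** The Methods part of the abstract names a control group without bruxism and then "group 2, children with bruxism treated with infrared light-emitting diode (LED); and group 3, bruxism treated with occlusal splint". The Groups section (1.3.1) repeats this: "Group 2: bruxism treated with infrared LED" and "Group 3: bruxism treated with occlusal splint". Neither place has a fourth group or a red light source.

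The Photobiomodulation treatment protocol section (1.5) reads differently. For Group 2 it says "During the same appointment, red LED" is given, at 650 ± 20 nm. It continues: "Group 3 will be submitted to the same analyses using an infrared LED protocol", at 850 ± 20 nm. It then adds: "The volunteers in Group 4 will be treated using the standard protocol of a rigid occlusal splint".

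Material and methods (section 3) starts from 16 per group, adds 20% for "possible dropouts (n = 19 per group), totaling 76 children and adolescents". Allocation procedure (1.3) uses envelopes numbered 1 to 76 in blocks of four, and each envelope holds a group assignment. Analysis of results (1.8) plans a two-way mixed ANOVA to test the treatment effect.

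**The concern.** The two descriptions cannot both be right. Two of the three listed labels change treatment between sections, and the splint moves to a label that the group list does not contain. The sentences are complete and carry distinct wavelengths and group numbers, so broken text extraction does not explain the difference.

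Three things depend on the answer. The envelope carries a group label, so the label determines what a child receives. The group factor in the ANOVA has three or four levels, depending on which section is followed. And if results are later reported for three groups, a reader could not tell a red-LED arm that was run and left out from a drafting slip.

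The arm in the trial's title is also under-described. The board of 6 LEDs, the operating time, the spot size and the output ("7-minute operation time, optical spot of" and the figures around it) appear only in the red-LED sentence. The infrared sentence gives a wavelength and a dose of 2.675 J/cm².

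**Working it through.** **Labels side by side**

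| Label | Abstract and Groups (1.3.1) | Treatment section (1.5) |
|---|---|---|
| Group 1 | no bruxism | not mentioned |
| Group 2 | infrared LED | red LED, 650 nm |
| Group 3 | occlusal splint | infrared LED, 850 nm |
| Group 4 | not listed | occlusal splint |

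No shown text says that an arm was dropped or maps one numbering to the other. The title, abstract, group list and Discussion name infrared as the test light; none mentions red.

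**Inputs for the total** (Material and methods): 16 per group, 20% added, 19 per group, total 76.

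1. Group size: 16 × 1.2 = 19.2, stated as 19.
2. Total = group size × number of groups.
   - Four groups: 4 × 19 = 76. This reproduces the stated figure.
   - Three groups: 3 × 19 = 57, which is 76 − 57 = 19 short.
3. Other three-group routes to 76:
   - without the dropout allowance, 3 × 16 = 48;
   - with 19.2 rounded up, 3 × 20 = 60;
   - with the minimum of 30 per group that the same section also states, 3 × 30 = 90;
   - working backwards, 76 / 3 = 25.3, not a whole number.

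So the total goes with the treatment section's numbering and not with the group list.

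**Does the block size settle it?** It depends on who is randomised.

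- If every label is randomised, as the abstract and Groups section literally say, 76 / 4 = 19 complete blocks fit four labels. A block of 4 over three labels gives 4 / 3 = 1.33 per label and cannot balance.
- Having no bruxism is a characteristic of the child and cannot be allocated, so only the treated arms can properly be randomised. The three-group list then has two such arms, and a block of 4 balances 2:2. The four-group layout has three, and a block of 4 does not balance.

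The block size therefore points either way and is not used as evidence.

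**Does the mention of 3 groups in the second sample-size calculation settle it?** No. It could mean the three listed groups or the three treated arms of section 1.5.

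**The case against.** The strongest defence is that section 1.5 carries text left over from a four-arm design, that the intended trial is the three-group one named in the title and abstract, and that the flowchart and SPIRIT figure, which are not shown, may display it. This may be so. But a figure could not make both printed texts true, and the leftover would extend to the total and the number of envelopes, which are working parts of the plan. Treating section 1.5 as a simple shift of labels also fails, because it contains an extra treatment with its own wavelength and settings.

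Three stronger readings are tempting, and the document does not support them.

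- *The number to recruit is undefined.* The total is 76 in the abstract, in Material and methods and in the envelope numbering. What is unclear is how many groups share it.
- *Blocks of four prove four groups.* As shown above, this holds only if children without bruxism are randomised too, which is not possible.
- *No child would receive a splint.* This would follow only if staff took labels from the Groups section and treatments from section 1.5. Either version followed alone contains an infrared arm and a splint arm, and a mixture would leave the Group 4 splint procedure with nobody to receive it, which staff would probably notice.

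The conflict in Material and methods between 19 and a minimum of 30 per group is a separate matter. It does not bear on how many groups there are.

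**Conclusion.** The point holds as an internal contradiction. Two of three listed labels carry a different treatment in section 1.5, one group there is absent from the group list, and the stated total exceeds the three-group total by 19 children (76 against 57). The label conflict rests on no assumption. The numerical part assumes only equal groups of the stated 19.

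The document does not show which layout is intended: the title, abstract, group list and Discussion favour three groups, while the total and the treatment instructions favour four. Because arm definitions and the sample size both depend on the answer, this must be corrected before the allocation list is used.

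**What to change.** Adopt one group list, with one label per treatment, in the abstract, Material and methods, Allocation procedure, Groups and the treatment section, and use the same list as the group factor in the ANOVA.

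- **If three groups are intended:** delete the red-LED arm; label infrared (850 nm) Group 2 and splint Group 3; state the board, operating time, spot size and output that apply to infrared; restate the total at 19 per group as 57.
- **If four are intended:** add the red-LED arm to the abstract and the Groups section, keep the labels of section 1.5, and keep 76.

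Under either list, randomise only the children with bruxism and recruit Group 1 as a non-randomised comparison group. With two treated arms, 2 × 19 = 38 envelopes are needed, and blocks of 4 work (nine full blocks and a final block of 2). With three treated arms, 3 × 19 = 57 envelopes are needed, in blocks of a multiple of 3 (19 blocks of 3, for example).

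The cost is a text correction and a newly generated allocation list. At 19 per group, neither option needs more children than the 76 already stated. Whether 19 or 30 per group governs has to be resolved separately, and the totals and envelope counts here would change with it.
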